### Activities

Based on the EMA survey four times a day, a decision will be made to randomize a participant to a JITAI or no JITAI based on the decision rules above. If participants are randomized to a JITAI, a message with a suggestion for an activity will be sent using m-path. The activities that will be suggested come from a “list of pleasurable activities”, which are part of the protocolized cognitive behavioral treatment for patients with a depressive disorder [36]. Examples of these activities include reading, singing, listening to music, walking, and gardening. These activities are divided into the following categories of life areas used in behavioral activation treatment protocols [5]: relationships, education/career, recreation/interests, mind/body/spirituality, and daily responsibilities. During the baseline period, participants rate how pleasurable or satisfying each activity on the list is on a scale ranging from not (0) to somewhat (1) to yes (2). Activities that are rated ≥ 1 on pleasure or satisfaction by the participant will have a follow-up question regarding the location (can this activity be performed when you are at home, outside or both?). For each participant, activities that they rated as pleasurable or satisfying and that can be performed at home, outside, or both will be selected as their personalized activities. Participants will also be prompted to choose at least one activity from each life area category. If randomized to receive a JITAI, participants will be asked which life category they prefer. After they indicate their preference, an activity will be randomly selected from their personalized activities in that category. The template used in m-path to suggest the activities will be evaluated during the course of the study and adapted based on feedback from the participants.

### Data management

Data from questionnaires and EMA assessments will be collected digitally and stored in a coded dataset accessible only to the research team. Interview transcripts will be pseudonymized. The key linking codes to identifying information will be stored separately. Data will be checked for completeness and consistency before analysis.

## Data analyses

### Design phase

#### Focus groups

The focus group data collected in the design phase will be thematically analyzed by two raters. The raters will first familiarize themselves with the data by carefully reading the focus group transcripts. They then will generate initial codes by identifying key concepts and ideas expressed by participants. Next, the raters will work together to group similar codes into potential themes. The raters will discuss discrepancies in their coding and theme development to reach consensus. Key themes that emerge from the analysis will be presented and serve as a basis for the m-path template. The experiences of the two patients and two therapists during the test will also be summarized, presented, and used to further improve the m-path template.

### Evaluation phase

#### Feasibility

Feasibility will be analyzed via descriptive statistics. We will calculate the dose-received adherence (= number of completed JITAIs divided by the total number of received JITAIs) for the complete length of the MRT, as the primary outcome. Additionally, we will divide the length of the MRT into four intervals of equal duration and calculate the dose-received adherence for each interval. This would provide more details regarding dose-received adherence during the study period.

#### Acceptance

Acceptance will be analyzed via descriptive statistics for the questionnaire data (CSQ, SUS, and TWEETS) and thematic analysis of the interview data.

#### Proximal outcomes

The effects of the JITAIs on the proximal outcomes will be analyzed with mixed-effects models. This type of model considers the nested structure of the data (e.g., multiple observations per individual per day) and adequately handles missing data [37]. In our primary analysis, we will examine the average proximal effect of delivering a JITAI (i.e., a message with an activity prompt) versus not delivering a JITAI (i.e., no message) on the depression scores (i.e., tailoring variables; average of the depression items), well-being scores (i.e., average of the two wellbeing items) at the next EMA and the daily step count, across participants and across randomized decision points. In a secondary analysis, we will examine whether the proximal effects of the JITAIs vary with time by examining the linear time trend of delivering a JITAI, assessed by estimating the interaction between the proximal effects of the JITAIs and the study day. Furthermore, moderation analyses will be conducted to evaluate whether the effect of JITAIs on the proximal outcomes depends on contextual factors by calculating the interaction effects between the intervention and contextual factors (i.e., situation: alone, with other people, at home, or outside). Sensitivity analyses will be performed by adding patient sex, age, symptom severity at baseline, and EMA survey depression item scores as covariates to the unadjusted model.

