### Proximal outcomes

#### Ecological Momentary Assessment (EMA) survey

A total of 16 questions are included in the EMA questionnaire (see Table 1). The morning questionnaire begins with an assessment of rest (I feel rested) rated on a scale ranging from not at all (1) to very much (7). Four items assessing depressive symptoms, which are based on the PHQ-9, are related to mood and energy level (i.e., “I feel down”; “I feel tired”; “I feel listless”; “I feel energetic”) and two items concerning well-being (“I feel satisfied”; “I feel cheerful”) [27]. These mood and well-being items are also rated on a scale ranging from not at all (1) to very much (7). These momentary mood and energy items also serve as tailoring variables at decision points during the MRT. Importantly, these tailoring variables indicate vulnerability or opportunity states in which withdrawal or avoidance is more likely and external prompting may facilitate the start of a feasible activity, consistent with an activation-first behavioral activation model. Additionally, participants are asked about their current location (e.g., at home, at school), who they are with (e.g., alone, with family), what activity they were doing before the measurement (e.g., studying, working), and how they rate that activity on a scale from very unpleasant to very pleasant. In subsequent EMA assessments after the first one of the day, participants are asked if they performed a suggested activity (yes/no). If they answer no, they are asked for the reason (e.g., did not feel like it, did not have energy, was not convenient, or other). If they answer yes, they rate how pleasant the activity was (very unpleasant to very pleasant) and how much satisfaction it provided (none at all to very much). The evening questionnaire includes additional items: an assessment of overall activity level during the day on a scale from not active at all (1) to very active (7), an evaluation of the best moment of the day on a scale from very unpleasant to very pleasant, and an open field for comments. The evening survey serves as a reflection on the day rather than as a decision point (see procedure). Finally, daily step counts are passively collected once a day via the participants’ smartphone sensors, as higher daily step counts are an indication of improvement in depressive symptoms [28].

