They will complete baseline questionnaires (PHQ-9, MHC-SF, QPR, and EQ-5D) and undergo a 1-week baseline period with two EMA surveys per day following a semi-random sampling in time blocks of 1 h (e.g., 09:00–10:00; 12:00–13:00; 15:00–16:00, and 18:00–19:00). Each assessment takes place at random moments in one of the time blocks, and scheduling of the time blocks is decided by the participants at the start of the baseline. After the baseline period, the intervention phase (MRT) will start and last 6 weeks. During the MRT, participants receive four EMA surveys per day—following semi-random sampling in time blocks of 1 h—which serve as a decision point. At each decision point, the participant is eligible for randomization if they (1) completed the EMA and (2) met a prespecified tailoring-variable threshold indicating that they are in the symptomatic half of the item scale (i.e., a vulnerability state for withdrawal/avoidance). Because the EMA includes both negatively and positively valenced items, thresholds are operationalized in a directionally consistent way: for negatively valenced symptom items (e.g., “I feel down,” “I feel tired,” “I feel listless”), eligibility is defined as a score ≥ 4; for positively valenced functioning items (e.g., “I feel energetic”), eligibility is defined as a score ≤ 4. This threshold was selected to identify "moderate-or-worse" vulnerability states where the risk of avoidance is elevated [35] while managing participant burden by preventing prompting during mild or asymptomatic states. If the decision point is eligible for randomization, there is a 50% probability of receiving a JITAI and a 50% probability of receiving no JITAI. Thus, randomization occurs repeatedly within participants across eligible decision points. Allocation to the TAU + JITAI and TAU groups is not randomized. Within the TAU + JITAI condition, randomization at eligible decision points is generated automatically by m-path (simple randomization), and recruiters do not have access to future assignments. Because of the nature of the intervention, participants, therapists, and researchers are not blinded to study condition; therefore, no formal blinding or unblinding procedures apply.

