#### Sample size

The primary feasibility outcome is dose-received adherence, defined as the proportion of completed JITAIs among all received JITAIs during the MRT phase. A sample size calculation for this outcome was based on the precision of the estimated proportion of completed JITAIs among received JITAIs [39]. Because adherence was defined at the JITAI level, with repeated observations nested within participants, the calculation was adjusted for within-participant correlation using a design effect [40]. During the 6-week MRT phase, participants can have up to 168 decision points (42 days × 4 per day). Assuming participants are available at 66% of these moments and a probability of 25% of receiving a JITAI at a given decision point, participants are expected to receive approximately 28 JITAIs on average. Assuming an adherence proportion of 0.60, a two-sided 95% confidence interval, an average of 28 received JITAIs per participant, and a within-participant intraclass correlation of 0.05, 46 participants would yield an approximate confidence interval half-width of 0.041.

We set the recruitment target for the TAU + JITAI group at 52 participants, comprising the 46 participants indicated by the feasibility-based precision estimate plus 6 additional participants to allow for 13% dropout observed in samples with depression [41]. For consistency in the nonrandomized comparison, we will recruit an equal number of participants in the TAU group. The proximal and distal outcome analyses are intended to provide preliminary estimates to inform a future trial.

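### Daily step count is analysed per randomised decision point although it exists only once per day; under day nesting the fit would collapse to a zero effect

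*Protocol article*

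**What the plan says.** All references are to the Protocol article.

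- **Measurement.** Under Measures, EMA survey: "daily step counts are passively collected once a day". There is one value per participant-day.
- **Randomisation.** Under Procedure, Evaluation phase: "During the MRT, participants receive four EMA surveys per day", and each of these is a decision point. If the point is eligible, "there is a 50% probability of receiving a JITAI and a 50% probability of receiving no JITAI", and "randomization occurs repeatedly within participants across eligible decision points".
- **Analysis.** Under Data analyses, Proximal outcomes, the average effect of delivering or not delivering a prompt is estimated on the depression and well-being scores "at the next EMA and the daily step count, across participants and across randomized decision points". The models are mixed-effects models, a type that "considers the nested structure of the data (e.g., multiple observations per individual per day".

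The section gives no day-level exposure for steps. It does not list the random effects, and it does not say how a daily total is to be linked to the decision points of that day.

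**The concern.** For the EMA scores the unit works: each randomised point is followed by its own next survey. For steps it does not. A day with two or more randomised points has several exposures and one outcome. Someone implementing the sentence literally would copy the day's total to each randomised point. On a day with both a prompted and an unprompted point, the two arms then carry the same number.

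Step count is the only proximal outcome that does not rest on self-report, in a trial where participants know whether they were prompted. The Sample size section says the proximal estimates are meant to inform a future trial. An estimate that a routine modelling choice can push to zero would misinform it.

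**Working it through.** **The plan's own figures.** The article gives no figure for the step analysis. Its only calculation concerns adherence, and it reproduces: 168 × 0.66 × 0.25 = 27.7, or about 28 JITAIs; design effect 1 + 27 × 0.05 = 2.35; half-width 1.96 × √(0.24 × 2.35 / (46 × 28)) = 0.041, as stated. Its inputs serve below to gauge how often a day holds several randomised points.

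**Randomised points per day.** The section states: "Assuming participants are available at 66% of these moments and a probability of 25% of receiving a JITAI at a given decision point". With 50:50 assignment, a 25% chance of a prompt implies that 0.25 / 0.50 = 50% of available points are randomised. The chance that a decision point is randomised is then q = 0.66 × 0.50 = 0.33, or 4 × 0.33 = 1.32 points per day. Assuming independence between points, the number K per day is Binomial(4, 0.33):

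| K | 0 | 1 | 2 | 3 | 4 |
|---|---|---|---|---|---|
| Probability | 0.202 | 0.397 | 0.293 | 0.096 | 0.012 |

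- Days with K ≥ 2: 0.293 + 0.096 + 0.012 = 0.40.
- Share of randomised points on such days: (2 × 0.293 + 3 × 0.096 + 4 × 0.012) / 1.32 = 0.70.
- Days with both a prompted and an unprompted point: Σ P(K) × (1 − 2 × 0.5^K) = 0.293 × 0.5 + 0.096 × 0.75 + 0.012 × 0.875 = 0.23.

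**Day nesting on a repeated total.** Let Y_d be the total on day d and A_dj the assignment at point j. The within-day estimate is Σ(A_dj − mean A_d)(Y_d − Y_d) / Σ(A_dj − mean A_d)² = 0, whatever the true effect. A model with a day random intercept weights this zero against the between-day contrast. Rows of the same day are identical, so the likelihood keeps rising as the residual variance shrinks, and the zero takes all the weight.

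**Simulation.** It used 46 participants and 42 days, with K as above. Assumed values, not in the document: true effect 300 steps per prompt, between-person SD 2000, between-day SD 2500.

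One data set, participant and day variances held fixed:

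| Residual SD | Estimate | Log-likelihood |
|---|---|---|
| 1000 | 101 | −19858 |
| 300 | 11.7 | −18685 |
| 100 | 1.3 | −17617 |
| 10 | 0.013 | −15376 |
| 1 | 0.0001 | −13136 |

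When all variances were estimated (one data set), the effect was 7e-08 and the residual variance 0.0007.

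Over 60 runs:

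| Model | Mean estimate | Empirical SD | Mean model SE |
|---|---|---|---|
| Total repeated, participant intercept only | 278 | 99 | 99 |
| One row per day, number of prompts, adjusted for K | 284 | 101 | 101 |

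The simulation error of these means is about 100 / √60 = 13, so both are compatible with 300.

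**Adjustment for K.** The second model was harmless here only because K was drawn independently of assignment. In the trial, eligibility needs a symptomatic score and prompts are meant to improve mood, so an early prompt can change the later count. In further simulations (true effect 300) mood drove both eligibility and steps. When a prompt lowered later eligibility by 10 percentage points, the estimate was about 194 adjusted for K and about 276 unadjusted. Two other assumed settings gave 236 and 59 adjusted, against 288 and 245 unadjusted. Part of the unadjusted shortfall from 300 is genuine, since a prompt that lowers later eligibility also means fewer later prompts.

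**The case against.** A reader might infer that the trial, as planned, will report no step effect whatever the truth. The article does not support that. Zero requires both that the total is copied to each point and that the model has a day-level effect, and neither is stated. The nesting remark is general, marked as an example, and covers all proximal outcomes. A participant-only model is equally compatible with the text and recovers the effect with a calibrated standard error. The one-row-per-day model was no more precise (SD 101 against 99). A collapsed residual variance would probably also alert an analyst that something had gone wrong.

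A reader might also infer that steps walked before the prompt bias the result. They do not: given eligibility, assignment is 50:50 and independent of earlier steps, so these steps add noise. The day-level analysis keeps them too.

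Finally, this is a condensed article, and random-effect terms may properly be left to an analysis plan. That disposes of any complaint about unlisted random effects. It does not dispose of the unit: the article itself assigns step count to the decision-point analysis, and an analysis plan that follows it would inherit the mismatch.

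**Conclusion.** The point holds as a mismatch between the outcome and the stated unit of analysis, with a conditional consequence. If the total is repeated and the model nests within days, the effect is zero by algebra and does not depend on the assumed step variances or effect. With a participant intercept only, it is not forced to zero. The figures of 40% of days with several randomised points and 23% with mixed assignment rest on the protocol's 66% and 25%, on 50:50 assignment, and on independence between points. The size of the bias from adjusting for K rests on assumed values; its direction follows where low mood raises eligibility and lowers steps and prompts reduce later eligibility.

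The point is worth correcting but does not touch the primary outcome, which is feasibility. Steps are one of three proximal outcomes, and the proximal analyses are declared preliminary.

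**What to change.** In Data analyses, Proximal outcomes, take step count out of the analysis over randomised decision points and give it its own sentence:

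- One row per participant-day.
- Exposure: the sum, over that day's randomised points, of (assigned − 0.5), with assigned coded 1 for a prompt and 0 for none.
- A participant random intercept, with the previous day's steps as a covariate; these precede all of the day's assignments.
- No adjustment for the same day's number of randomised points, because earlier prompts that day can affect it.
- Sensitivity analysis: exposure defined by assignment at the day's first randomised point only.

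This changes wording only; no data collection or sample size is affected. The cost is interpretive: the estimate is a per-day dose effect and not a per-prompt effect, and should be reported as such.

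### The primary proximal model omits the momentary score taken just before each randomisation: no bias, but some precision is given up on the two EMA outcomes

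*Protocol article*

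**What the plan says.** In the protocol article, under Proximal outcomes in the data analyses, the method is fixed as follows: "The effects of the JITAIs on the proximal outcomes will be analyzed with mixed-effects models". The main contrast is then named: "In our primary analysis, we will examine the average proximal effect of delivering a JITAI" against not delivering one. The outcomes are the depression and well-being scores at the next EMA, and the daily step count. Covariates appear only at the end of that section, where the sensitivity analyses consist of "adding patient sex, age, symptom severity at baseline, and EMA survey depression item scores as covariates to the unadjusted model". The primary model is therefore the unadjusted one. No reason is given.

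The Evaluation phase section of the Procedure sets the conditions for randomisation: "the participant is eligible for randomization if they (1) completed the EMA and (2) met a prespecified tailoring-variable threshold". At an eligible point "there is a 50% probability of receiving a JITAI and a 50% probability of receiving no JITAI". The section on the EMA survey says of the symptom items: "These momentary mood and energy items also serve as tailoring variables at decision points during the MRT". The same items, averaged, form the depression outcome at the next prompt. The two well-being items are part of the same survey.

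**The concern.** The design supplies a good covariate at no extra burden. It is measured immediately before allocation, it is complete at every randomised point, and it uses the same items as the outcome a few hours later. If momentary mood carries over between prompts, this score explains part of the residual variation in the within-person contrast. Sex, age and baseline severity are constant within a person and explain little of it.

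The plan puts the momentary depression score in a sensitivity analysis and does not list the momentary well-being score at all. What is at stake is the width of the interval around the proximal effect. The Sample size section describes the proximal results as preliminary estimates to inform a future trial, so their precision is much of their value.

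**Working it through.** **What the plan itself computes.** The article gives no precision or power figure for the proximal effect. Its only such figures concern adherence, and they reproduce:
- Expected JITAIs per participant: 168 × 0.66 × 0.25 = 27.7, stated as about 28.
- Design effect: 1 + (28 − 1) × 0.05 = 2.35.
- Half-width: 1.96 × √(0.60 × 0.40 × 2.35 / (46 × 28)) = 0.041, as stated.

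None of this bears on the JITAI contrast, so the gain from adjustment has to be worked out separately.

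**Inputs from the article.** 46 participants; 168 decision points each; 66% EMA completion; eligibility restricted to the symptomatic half of the scale; allocation probability 0.5.

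**Assumed inputs, not in the article.** Lag-1 within-person autocorrelation 0.2 to 0.6; between-person share of the score variance 0.3 or 0.5; true effect −0.10 on a standardised score.

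**Formula.** In a within-person comparison with constant 50:50 allocation, the ratio of adjusted to unadjusted variance is 1 − r². Here r is the within-person correlation, among eligible points, between the decision-point score and the next score. Eligibility truncates the decision-point score, so r is smaller than the autocorrelation.

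**Depression.** Simulation with a within-person estimator, 1,500 runs per setting. Paired values are for a between-person share of 0.3 / 0.5. The last column is 1 − (SE ratio)².

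| Autocorrelation | Variance cut without truncation | r among eligible points | SE ratio | Variance cut |
|---|---|---|---|---|
| 0.2 | 4% | 0.125 / 0.135 | 0.992 / 0.991 | 1.6% / 1.8% |
| 0.3 | 9% | 0.195 / 0.210 | 0.981 / 0.978 | 3.8% / 4.4% |
| 0.4 | 16% | 0.266 / 0.287 | 0.964 / 0.958 | 7.1% / 8.2% |
| 0.5 | 25% | 0.342 / 0.366 | 0.940 / 0.930 | 11.6% / 13.5% |
| 0.6 | 36% | 0.426 / 0.454 | 0.905 / 0.890 | 18.1% / 20.8% |

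At 0.3 to 0.5 the variance cut is about 4 to 14%. On the standard error that is 1 − √0.96 = 2% to 1 − √0.86 = 7%. A separate simulation with a participant random intercept gave variance ratios of 0.953 at 0.3 and 0.855 at 0.5, which agrees.

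**Bias.** Mean estimates were −0.0985 to −0.1007 unadjusted and −0.0985 to −0.1017 adjusted, against a true −0.10. Neither model is biased.

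**Well-being.** Eligibility acts on depression items. If momentary well-being correlates with them, it is truncated indirectly. With an assumed within-person correlation of −0.5 to −0.8, the variance cut is:
- about 6 to 7% at autocorrelation 0.3, and 1 − √0.94 = 3% to 1 − √0.93 = 4% on the standard error;
- about 17 to 21% at 0.5, and 1 − √0.83 = 9% to 1 − √0.79 = 11% on the standard error.

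In round terms this is 7 to 20% of the variance.

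**Sensitivity to the truncation model.** The depression table truncates the outcome score itself. In the plan, eligibility rests on selected items while the outcome is an average of items, so truncation may be lighter. With one tailoring item and an assumed inter-item within-person correlation of 0.5, the depression cut was 6% at 0.3 and 17% at 0.5. The order of magnitude is the same.

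**The case against.** The case for leaving the plan alone has four parts.

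1. The unadjusted model is valid, and an adjusted depression analysis is already planned. The change mostly swaps which model is called primary. That is true for depression; for well-being, no model lists its own prior score.
2. The trial's primary outcome is descriptive feasibility, and the sample size rests on it alone. No decision rule depends on the width of a proximal interval. This stands and limits the severity.
3. The gain is modest and depends on an autocorrelation the article does not give. This also stands; at 0.2 the standard error for depression falls by only about 1%.
4. The covariate is a lagged outcome that earlier prompts can affect, in a model with a participant random effect. Some trial mixed-model fits gave convergence warnings, which is why the table uses a within-person estimator. The adjustment therefore needs some care in specification.

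A reader might also infer more than the article supports:
- **That the unadjusted estimate is biased.** Constant 50:50 allocation rules this out, and the simulation confirms it.
- **That the EMA depression covariate might be the next-EMA score, which is the outcome.** The covariate wording does not state the timing, but an article may leave that detail to the full plan. The EMA survey section places these items at decision points.
- **That the well-being gain is the full 1 − r², or 9 to 25% at 0.3 to 0.5.** That would require well-being to be nearly uncorrelated with the depression items that determine eligibility.
- **That every proximal outcome can be adjusted in this way.** Step count is collected once a day and has no decision-point value.

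**Conclusion.** The point holds as one of efficiency. The primary proximal model leaves out a covariate that is complete by design, and the well-being pre-score is in no listed model. Validity is not affected. The sizes in the working for autocorrelation 0.3 to 0.5 are conditional on that assumed range, on the assumed depression–well-being correlation and on the truncation model; they are not properties of this trial's data. Severity is low, because the outcomes concerned are preliminary and not primary.

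**What to change.** In the Proximal outcomes analysis section, for the two momentary outcomes only:
- adjust the primary model for next-EMA depression for the depression score at the decision point, and the model for next-EMA well-being for the well-being score at the decision point, both measured before randomisation;
- code treatment centred at its known probability of 0.5, because the covariate is a time-varying lagged outcome, and check convergence;
- keep the unadjusted model as the sensitivity analysis.

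Leave the daily step-count model outside this change.

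The cost is a sentence or two of analysis wording and slightly more care in fitting. No new data, participants or burden are needed. Settling it before the data are seen also removes a later choice between adjusted and unadjusted results.
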